### Study Procedures

#### Enrollment

Participant enrollment begins before 5 months of age. Interested participants are screened by phone or email; if eligible, an in-person baseline visit is scheduled and informed consent is obtained at the baseline visit. Enrollment of eligible infants take place over the first 4 years of the study. As part of the informed consent process, participants are notified that they may withdraw at any time and of the actions that may deem the infant ineligible for the study. At time of enrollment, each participant is assigned a unique study-ID (MINT-001 through MINT-300) for subsequent data collection.

#### Randomization

Upon enrollment, participants are randomized into one of four groups, differentiated by source of protein-rich foods they consume (meat, dairy, plant or control group). A stratified random sampling design is used where the strata are defined by mode of feeding (breastfed or formula-fed), sex (male or female) and mode of delivery (cesarean or vaginal delivery). The four feeding groups are randomized within each strata in groups of four so each diet (Meat, Dairy, Plant, Reference) occurs exactly once per four enrollments. Given our rolling recruitment strategy over 4 years, this ensures that the initial randomization of group within each strata is close to balanced and that there is little to no relationship with the order of recruitment. A stratified randomization design controls for possible confounding variables and results in an increase in power.

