## Methods

### Study Design

This is a randomized controlled feeding trial with four groups. After screening, eligible participants and their caregiver(s) will visit the Clinical & Translational Research Center (CTRC) at Children's Hospital Colorado (CHCO) to complete the baseline visit (Figure 1) at 5 months of age. After obtaining informed consent, participants will be assigned and randomized to one of the four study diets: (1) a meat-protein-predominant diet group (Meat); (2) a dairy-protein-predominant diet group (Dairy); (3) a plant-protein-predominant diet group (Plant); or (4) a reference group without intervention (Reference).

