### Timeline and Milestones (in Months, Commencing March 1, 2021)

0–5 Study preparations: Manuals of operation, IRB approval, Children's Hospital Colorado Research Institute Approval and Clinicaltrials.gov registration.6–48 Enrollment of 260–300 eligible participants and complete all baseline visits.21 Completion of 50% participants in each group complete.54 All clinical procedures complete.60 Laboratory analyses of blood, urine and stool analyses, data analyses complete.

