### Participants

Participants are being recruited in the metro Denver area from households with 3–4 month-old infants via direct mailing by Colorado Department of Public Health & Environment (CDPHE) which has access to the birth registry. Up to 300 infants will be recruited (75/group) to have at least 240 completers (60/group), based on a conservative estimate of 20% attrition.

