### Follow-Up Procedures: Home Visits

Monthly home visits at ages 6, 7, 8, 9, 10, and 11 months of age (±7 days) are conducted for each participant by one or two study coordinators. At each home visit, coordinators collect the following: stool sample (pre-collected by parents within 48 h before the visit), anthropometric measures (weight, length, head circumference), health questionnaire, 3-day diet record, food intake log, and breastmilk collection if the participant consumes breastmilk. The 9-month diet record is a weighed 3-day diet record. Caregivers also conduct test weighing again at 9 months if the participants consume breastmilk. Study coordinators also deliver study food (intervention groups) or food voucher (reference group) at the visit. Growth parameters are plotted on the infant's growth chart and Z-scores are calculated.

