### Risks

The study protocol is expected to have minimal risk because there are no invasive procedures except the three blood draws at 5, 12, and 24 months of age, which are necessary to answer the research question. The 12-month blood draw will include analyses (Pb and Hb) routinely obtained for well-child surveillance; results will be provided to the primary care provider to avoid a second clinical blood draw. There is an unlikely risk of food allergies. During screening, the caregiver is asked if the infant has any food restrictions or allergies, including milk/dairy protein allergies (i.e., on a special formula). If the answer is yes, the infant is not eligible to participate. If the participant has no food restrictions or allergies, he/she is unlikely to be allergic to the complementary foods provided because most of the study foods are not considered highly allergenic foods. At the baseline visit, the study coordinator explains the potential risk of allergy development when starting complementary feeding and caregivers are given a list of common signs of food allergies. Food allergy is closely monitored by monthly health questionnaires. If repeated concerns are expressed, the participant will be removed from the study and advised to consult the primary care physician.

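### Constant blocks of four within strata would let staff who track earlier allocations foresee about a quarter of assignments; block sizes should vary for blocks not yet used

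*Protocol article*

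**What the plan says.** The Randomization section of the protocol article stratifies by feeding mode, sex and delivery mode, each with two levels. Within strata the diets are "randomized within each strata in groups of four so each diet (Meat, Dairy, Plant, Reference) occurs exactly once per four enrollments". The section justifies this by near-balance within strata, and little relation to recruitment order, over four years of rolling recruitment.

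Other sections bear on who could see the sequence and when:

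- **One centre.** Under Study Design, families "will visit the Clinical & Translational Research Center (CTRC) at Children's Hospital Colorado (CHCO) to complete the baseline visit". The same section places randomization after informed consent.
- **Coordinators see the arm.** Under Follow-Up Procedures: Home Visits, "Study coordinators also deliver study food (intervention groups) or food voucher (reference group) at the visit".
- **A coordinator is present at enrolment.** Under Risks, "At the baseline visit, the study coordinator explains the potential risk of allergy development". The Enrollment section places consent at that same visit.
- **Blinding.** Under Anthropometric Measurements, the pediatric nurses at the research centre are blinded. No other role is described as blinded.
- **Numbers.** Under Participants, "Up to 300 infants will be recruited (75/group) to have at least 240 completers (60/group), based on a conservative estimate of 20% attrition". The Timeline section gives a range: "Enrollment of 260–300 eligible participants and complete all baseline visits".

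**The concern.** A block is predictable when three things hold: its size is known, its composition is known, and earlier assignments can be seen. The article fixes and publishes the first two. Unblinded delivery of food or vouchers provides the third. The stratum of the next infant is no obstacle, because feeding mode, sex and delivery mode must all be known before assignment.

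If someone who influences entry knows that the next slot is, say, Plant, then the date of a visit, the encouragement given to a caregiver or a borderline eligibility judgement can come to depend on that diet. Some entry criteria leave room for judgement: the infant's general health, the ability to eat the study foods, and the caregiver's willingness to feed them. Selection of this kind would act on traits such as caregiver motivation or expected adherence. The baseline comparisons planned under Statistical Approach cover measured confounders and could miss it.

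**Working it through.** **Inputs.** Four arms; a constant block of four with each arm once (Randomization); 2 × 2 × 2 = 8 strata (Randomization); 260 to 300 infants (Timeline; Participants). The article states no predictability figure.

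**The plan's own figure.** 240 / (1 − 0.20) = 300 and 60 / (1 − 0.20) = 75 per group. The recruitment target reproduces, and the point here does not touch it.

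**Complete blocks, all earlier assignments in the stratum known.** The diets still possible at slots 1 to 4 number 4, 3, 2 and 1.

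- Certain assignments: only slot 4, so 1/4 = 25%, at most 300 / 4 = 75 infants.
- Slot 3 is narrowed to two diets.
- Best-guess success: (1/4 + 1/3 + 1/2 + 1) / 4 = 2.083 / 4 = 52.1%, against 25% by chance.

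**Incomplete final blocks.** A stratum with *n* infants has floor(*n*/4) certain assignments. If a final remainder of 0, 1, 2 or 3 is about equally likely, its mean is 1.5 per stratum, or 8 × 1.5 = 12 infants in total.

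- N = 300: (300 − 12) / 4 = 72, or 24.0%.
- N = 260: (260 − 12) / 4 = 62, or 23.8%.
- Best guess: a remainder of 0, 1, 2 or 3 adds 0, 0.25, 0.583 or 1.083 correct guesses, mean 0.479. For N = 300 this gives (72 × 2.083 + 8 × 0.479) / 300 = 153.8 / 300 = 51.3%. For N = 260 it gives (62 × 2.083 + 8 × 0.479) / 260 = 133.0 / 260 = 51.2%.

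Simulation agrees: 24.0% certain at N = 300 (range over replicates 23.3% to 24.7%), 23.8% to 23.9% at N = 260, and about 51% best-guess success at both. The article gives no stratum mix, so three were assumed: equal strata; 70% breastfed with 30% cesarean; 80% breastfed with 20% cesarean. The results barely differ.

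**Effect of varying the block size.** Simulated for N = 300 and 8 equal strata, in the worst case where staff know the size of each block:

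| Block sizes | Certain | Best guess |
|---|---|---|
| 4 only (current) | 24% | 51% |
| 4 or 8 | 17% | 48% |
| 4, 8 or 12 | 13% | 45% |
| 8 or 12 | 10–11% | 44% |

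If the sizes are concealed, the certain share is lower still.

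**The case against.** The strongest reply is that foresight is conditional and that the step from foresight to selection is not documented.

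- **Tracking.** Someone would have to know the allocations, in order, in each of 8 strata over about four years. Home visits are made by one or two coordinators per participant, and nothing says that any one of them sees every infant. This stands: full tracking is feasible at one centre but is an inference.
- **Control of entry.** A reader might infer that coordinators decide who enters. The article does not say so. It has a coordinator explain allergy risk at the baseline visit, and does not say who screens, judges eligibility or takes consent. The full protocol may settle this and may describe concealment of the list. Concealment alone would not help, because the next diet follows from the published block size and the visible arms, not from sight of the list.
- **Room to steer.** Recruitment is by mailing through the state health department, screening is by phone or email, most criteria are factual, and the visit is tied to 5 months of age. This narrows the scope without removing it.
- **Safeguards in place.** Allocation already follows consent, and the nurses measuring at baseline are blinded. Both help. Neither prevents a guess made before the visit.
- **Validity.** A block equal to the number of arms is a legitimate design, and the article gives its reason. This also stands: nothing in the planned analysis is wrong because of it.

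**Conclusion.** The point holds as a conditional and modest weakness. If staff track earlier allocations within strata, about 24–25% of assignments can be foreseen with certainty and about 51–52% guessed correctly, against 25% by chance.

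Two stronger readings are tempting. One is that a quarter of assignments are in fact foreseen. The other is that the growth or microbiota comparisons are biased. The documents support neither: they show that prediction is possible, not that anyone tracks the sequence or acts on it. The percentages measure guessability and do not translate into a shift in any outcome.

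The conclusion rests on the block being constant as described, on arms being visible to coordinators through delivery, and on one team working at one centre. It is worth acting on because the change is cheap and few roles in the trial are described as blinded.

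**What to change.** **For blocks not yet used:**

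1. Draw the block size at random within each stratum, for example from 4 and 8, or from 4, 8 and 12. The wider set gives more protection if sizes leak (13% certain rather than 17%).
2. Keep the new sizes out of every document that enrolling staff see until accrual ends. Much of the gain depends on this.
3. Release each allocation only after the baseline measurements are recorded. Study Design already places it after consent, so only this step is new. State which measurements count, since the post-dose urine collection continues at home for seven days after the visit.

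**For blocks already used:** report the constant block of four as a limitation, and say who could see earlier allocations and who enrolled.

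**Cost:** a new list for the remaining allocations, and slightly larger possible imbalance within a stratum at the end of accrual. Strata average 300 / 8 = 37.5 infants, so this should stay small with the sizes named. The Timeline schedules enrolment to month 48 from March 2021, that is, to about March 2025. Few or no blocks may therefore remain, in which case only the reporting step applies. The documents do not show actual progress.

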#### Baseline Data to Be Collected Includes

##### Demographic Information

Study participants are given a questionnaire at the baseline visit to report both the infant and parental ethnicity, race, gender, high-risk behaviors such as smoking tobacco or other recreational drugs, education level, and gross family income.

##### Infant and Paternal Health History

Another questionnaire is given to the caregiver to discuss birth details such as mode of delivery and infant weight and length. Caregivers are asked to disclose the family health history of the following: obesity, cardiovascular disease, type 2 diabetes mellitus, and allergies in immediate family members. Infant feeding habits for the previous month are also assessed in addition to any illness, medication, supplements, or antibiotic use. This infant health questionnaire is to be repeated at each subsequent monthly home visit.

##### Anthropometric Measurements

Pediatric nurses at the CTRC, who are blinded to the treatment groups, obtain three measurements of weight in kilograms, three measurements of length in centimeters, and three measurements of head circumference in centimeters. Study coordinators calculate the average measurement as the baseline anthropometrics for the participant. Parental self-reported height and weight measurements are also to be obtained at this visit.

##### Dietary Intake

A weighed 3-day diet record is collected from caregivers before the intervention begins. A kitchen scale and calibration weight, plus the diet record with instructions, are provided to caregivers. For breastfed infants who do not use bottles, testing weighing using Seca^TM^ 757 infant scale is conducted before and after each feed during the 3 days when the 3-day diet record is filled out. Registered dietitians from the research team train parents/caregivers to fill out the diet record.

##### Biospecimen Samples

At the baseline visit, pediatric nurses at the CTRC draw blood from all able participants via venipuncture (3–5 ml). Samples are centrifuged, and serum is stored at −80°C until analyzed. Individual aliquots will be used to measure ICF-1, ICFBP3, insulin, blood lipids (triglycerides, HDL, LDL and total cholesterol), alpha 1-acid glycoprotein (AGP), high sensitivity C-reactive protein (CRP), and quantitative amino acids. After the baseline visit at the Children's Hospital Colorado CTRC, urine samples (one pre-dose and seven post-dose) are collected by the caregiver to assess total energy expenditure and two-compartment body composition using the doubly labeled water technique (29). Urine samples are collected by placing cotton balls in the diaper and after soaked with urine, cotton balls will be placed in the barrel of a 20 ml sterile syringe and urine will be expressed into a sterile plastic tube. A stool sample is also collected from participants' homes for gut microbiota analysis. Stool samples are collected by placing a diaper liner in the infant's diaper, which allows urine to pass and stool to stay. Caregivers are advised to collect the soiled diaper liner and keep it in the home freezer before the study coordinator retrieves it. Lastly, a fasting breastmilk sample is collected from caregivers who are breastfeeding. Macronutrient and energy profiles of breastmilk are assessed via mid-infrared spectroscopy (Human Milk Analyzer, Miris, Uppsala, Sweden). Detailed instructions on how to collect urine, stool and breastmilk samples, and sample collection kits are provided to caregivers.

### Dietary Intervention

Participants in the three intervention groups are asked to avoid protein-rich foods from other assigned groups (30) and consume protein only from their assigned group. All complementary foods, including infant cereal, low-protein fruits and vegetable purees, and designated protein-rich foods are provided to the three intervention groups. For formula-fed infants, the same brand cow-milk based infant formula is provided. The most recent NHANES report showed that the median protein intake of US infants 6–11 months (31) is 10% total energy or 2.5 g/kg/d. This quantity is used as the targeted total protein intake. Caregivers of infants in the reference/control group are given compensation to purchase complementary foods. Based on weight recorded at the visit and the reported formula/breastmilk intake, a recommended amount of meat- dairy- or plant-based food will be provided to caregivers to approximate a total protein intake of 2.5 g/kg/d. This estimation is updated every month. A sample diet plan is in Table 1, based on a formula-fed infant with a 60th percentile weight-for-age at 9 months.

**Table 1 T1:** Examples of diet plans for the three intervention groups^a^.

	**Food item**	**Protein**	**Calorie**
Total	Total calorie needs		~650 kcal/d
	Total protein (2.5 g/kg/d)	21 g/d	84 kcal/d
Formula (not restricted)	Formula 18 ounces	9 g/d	400 kcal/d
Dairy group^b^	1 Yogurt (Yobaby^®^)	4 g/d	80 kcal/d
	Cheese (shredded) (Horizon^®^)	6.5 g/d	80 kcal/d
	Others (e.g., 1 Beech Nut^®^ zucchini and banana blend; or one servicing of fortified rice cereal)	1 g/d	
Meat group^b, c^	1.5 jar of ham and gravy (Gerber^®^)	10 g/d	80 kcal/d
	Others (e.g., 1 Beech Nut^®^ zucchini and banana blend; or one servicing of fortified rice cereal)	1 g/d	
Plant group^d^	1.5 vegetable pouch (e.g., Ella's kitchen^®^ four bean feast)	5 g/d	90 kcal/d
	1.5 vegetable pouch (e.g., Earth's best^®^ spinach lentil)	5 g/d	50 kcal/d
	Others (e.g., 1 Beech Nut^®^ zucchini and banana blend; or one servicing of fortified rice cereal)	1 g/d	
Reference group	No restriction (observational group and will follow standard of care)		

a *These estimates are based on an exclusively formula-fed 9-month-old female with a 8.5 kg body weight which is ~60th percentile weight-for-age*.

b *Both Dairy and Meat groups are advised to avoid plant foods of relatively high protein contents (a list will be provided). Cheese will be shredded before providing to the infant*.

c *The Meat group is allowed to have fish. However, commercial fish-based infant foods are very rare and if parents choose to feed home-made fish to the participants, they will record the time, type and amount*.

d *Both dairy- and plant-based complementary foods have low iron content. Participants in all intervention groups are advised to consume one serving of iron-fortified cereal per day to meet their iron needs*.

### Follow-Up Procedures: Home Visits

Monthly home visits at ages 6, 7, 8, 9, 10, and 11 months of age (±7 days) are conducted for each participant by one or two study coordinators. At each home visit, coordinators collect the following: stool sample (pre-collected by parents within 48 h before the visit), anthropometric measures (weight, length, head circumference), health questionnaire, 3-day diet record, food intake log, and breastmilk collection if the participant consumes breastmilk. The 9-month diet record is a weighed 3-day diet record. Caregivers also conduct test weighing again at 9 months if the participants consume breastmilk. Study coordinators also deliver study food (intervention groups) or food voucher (reference group) at the visit. Growth parameters are plotted on the infant's growth chart and Z-scores are calculated.

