### Primary Outcomes

1) *Infant growth*

Pediatric nurses at the Children's Hospital Colorado CTRC (at baseline, 12 and 24 months) and study coordinators (at monthly home visits) obtain a series of infant anthropometric measurements. These measurements including weight (Seca^TM^ 337 infant scale), length (obtained in recumbent position using an infant stadiometer), and head circumference-for-age (Seca infant head circumference measuring tape). Growth Z scores are calculated using length and weight based on WHO/CDC standards (32).

2) *Body composition and total energy expenditure at 5 and 12 months of age*

At baseline and 12 months, a pre-dose urine sample is collected to document basal enrichment of ^2^H and ^18^O, then 0.1 g/kg body weight 99% enriched ^2^H_2_O and 0.3 g/kg 10% enriched H${}_{2}^{18}$O are orally administered. Caregivers are asked to collect one daily sample for 7 days post-dosing. Urine samples are analyzed for ^18^O and ^2^H enrichment by Off-Axis Integrated Cavity Output Spectroscopy (OA-ICOS, Los Gatos Research Inc., Mountain View CA) (33). Isotope dilution space will be calculated via the standard equation of pre-dose and zero-time intercept enrichment via back-extrapolation, which is validated in infants (34). Total body water will be calculated from dilution space × 1.04 to account for water exchange in non-aqueous tissues. Finally, total fat-free mass will be obtained from total body water ÷ age/sex-specific hydration factor (i.e., 79% for 6-month-old infants). CO_2_ production, obtained from the fractional turnover rates of ^2^H and ^18^O (35), is converted to total energy expenditure via Weir equation (36).

3) *Gut microbiota*

Caregivers will obtain a fresh stool sample each month of participation (5–12 months of age) and one at 24 months. 16S rRNA gene amplicon sequencing (37–39) will be performed on all samples to profile fecal bacterial communities. Following sequence QA/QC (37–39), 16S rRNA gene sequences are classified using the SINA/Silva classifier.

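### Home-visit growth measurements at 6–11 months are in effect unblinded, and the Aim 1 model does not separate them from the blinded clinic measurements

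*Protocol article*

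**What the plan says.** **Who measures at home.** The section on home visits states: "Monthly home visits at ages 6, 7, 8, 9, 10, and 11 months of age (±7 days) are conducted for each participant". The visiting team is one coordinator, or at most two. Among the items collected are "anthropometric measures (weight, length, head circumference), health questionnaire, 3-day diet record, food intake log". The same section adds: "Study coordinators also deliver study food (intervention groups) or food voucher (reference group) at the visit". The outcome section agrees on the assessors: "study coordinators (at monthly home visits) obtain a series of infant anthropometric measurements", while nurses at the clinic measure at baseline, 12 and 24 months.

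**Who is blinded.** The only blinding statement in the article is in the baseline section on anthropometry: "Pediatric nurses at the CTRC, who are blinded to the treatment groups". The 12-month visit is described as repeating the baseline procedures. No blinding, separate assessor or order of tasks is described for the home visits.

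**How the data are used.** Under Statistical Approach, Aim 1, LAZ and WLZ are modelled with diet, time and their interaction, with random effects by subject. Pairwise Tukey comparisons follow a significant interaction. The section does not say whether time is categorical or linear, and it treats nurse and coordinator measurements alike.

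**The concern.** Someone who brings one arm's foods, or the Reference voucher, and picks up the food log cannot be blind to the arm. The section on the dietary intervention links the tasks further, because the amount of study food is set from the weight recorded at the visit.

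Recumbent length depends on how the infant is positioned, so it is more open to an assessor's expectation than a scale reading. Length enters both LAZ and WLZ. If it is read slightly differently by arm at the home visits, the difference enters the interaction test for a primary outcome, and that test opens the pairwise comparisons. The blinded 5- and 12-month values are collected, but the growth analysis described under Aim 1 gives them no separate role. For the microbiota, by contrast, Aim 2 names both an end-of-intervention and a longitudinal analysis.

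**Working it through.** **1. Inputs from the article.** Home visits at 6, 7, 8, 9, 10 and 11 months; nurse visits at 5, 12 and 24 months; 60 completers per arm in four arms. The stated sample size reproduces: 60 / (1 − 0.20) = 75 per arm and 240 / 0.80 = 300 in total. The stated simulated power of 80–90% cannot be reproduced, because the pilot parameters are not given. The point does not depend on it.

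**2. Count by assessor.**
- 5 to 12 months: 6 of 8 time points = 75%
- After baseline, to 12 months: 6 of 7 = 86%
- Including 24 months: 6 of 9 = 67%
- Planned measurements in completers, 5 to 12 months: 240 × 6 = 1,440 of 240 × 8 = 1,920

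**3. Linear time, 5 to 12 months.** The leverage of a visit on the slope is (t − 8.5)² / Σ(t − 8.5)².
- All eight visits: Σ = 42
- Six home visits: 2 × (2.5² + 1.5² + 0.5²) = 17.5, so 17.5 / 42 = 42%
- Two nurse visits: 2 × 3.5² = 24.5, so 24.5 / 42 = 58%

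A constant shift b at the home visits in one arm changes the slope by b × Σ_home(t − 8.5) / 42 = 0, because the home visits are symmetric about 8.5. It still moves that arm's average level by 0.75b.

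Now let the shift grow as b(t − 5)/6, reaching b at month 11, and return to zero at the nurse visit. Then Σ(t − 8.5)(t − 5)/6 over the home visits is −0.417 − 0.500 − 0.250 + 0.333 + 1.250 + 2.500 = 2.917. The slope changes by 2.917b / 42 = 0.0694b per month, or 0.0694b × 7 = 0.49b over the 7 months.

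**4. Categorical time (illustration).** The article gives none of the following, so they are assumptions: no true effect, a constant shift d at months 6–11 in two of the four arms, random intercept only, residual SD 0.3–0.5 Z. With 60 per arm the interaction test has 3 × 7 = 21 and 236 × 7 = 1,652 degrees of freedom.

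The home-visit indicator centred on its mean has sum of squares 6 × 0.25² + 2 × 0.75² = 1.5. The arm indicator centred on its mean has sum of squares 4 × 0.5² = 1. The noncentrality is therefore λ = 60 × 1.5 × d² / SD².

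| d (Z) | SD 0.3 | SD 0.4 | SD 0.5 |
|---|---|---|---|
| 0.05 | λ = 2.5; 11% | λ = 1.4; 8% | λ = 0.9; 7% |
| 0.10 | λ = 10; 39% | λ = 5.6; 21% | λ = 3.6; 14% |

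The percentages are rejection rates of a nominal 5% test.

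**The case against.** **Absent detail may lie elsewhere.** The article is condensed. A supporting analysis may be in an unseen analysis plan, and task order at home visits may be in the manuals of operation. This stands as a caution, and the absence of either from the article is not itself the fault. But the article does fix who measures at home and what else that person does there, and no analysis plan changes that.

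**The trajectory result rests mainly on unblinded data.** A reader might infer this from the 75%. It holds by count, and for a model with categorical time. It does not hold for a linear slope over 5–12 months, where the two nurse visits carry 58% of the leverage. Time coding is not stated, so the stronger wording is not supported.

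**Large false-positive rates.** The arithmetic is sound, but the shift, the residual SD and the error structure are all assumed. A step at home visits would also tend to disappear at the nurse-measured 12-month visit, which would make it visible.

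**Bias in the hypothesised direction.** The primary hypothesis predicts lower WLZ in Meat and Plant and gives no direction for LAZ. Over-reading length lowers WLZ but raises LAZ, so the directional argument applies to WLZ only. The article does not say what coordinators know of the hypothesis. Nor does it say who handles the growth chart: "Growth parameters are plotted on the infant's growth chart and Z-scores are calculated" names no one.

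**Existing protection.** Doubly labeled water body composition at 5 and 12 months is listed among the primary outcomes. It is an independent check on adiposity, but not on LAZ or WLZ.

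**Open delivery is inherent in a food trial.** True, but this does not require the same person to deliver and to measure when two attend.

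**Conclusion.** The concern holds in a limited form. Six of the eight growth time points from 5 to 12 months are measured by staff who, by their other tasks at the visit, must know the arm. That they are unblinded is an inference, but a near-certain one. The Aim 1 model does not separate these points from the blinded ones, so there is a path for bias into the diet-by-time result.

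Its size cannot be fixed from the article. With categorical time, a constant home-visit shift feeds directly into the interaction; the 14–39% (0.10 Z) and 7–11% (0.05 Z) rates are illustrations on the assumptions stated. With linear time, a constant shift cancels and only a growing one matters, at about 0.49 of its month-11 value. The documents give no evidence that any such shift occurs, and do not support saying that the growth result is biased or must favour the hypothesis.

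**What to change.** 1. Pre-specify, as a supporting analysis, a baseline-adjusted comparison of LAZ and WLZ at 12 months that uses only the clinic nurses' measurements. Report it beside the trajectory model.
2. State in advance that a trajectory difference which this comparison does not support in direction will be described as resting on unblinded measurement. Agreement in size should not be required, since the two estimates differ in precision and no threshold is obvious.
3. At home visits attended by two coordinators, have the one who measures not handle the food or the logs.

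The cost is one further analysis of data already planned and a division of tasks among staff already present. The nurse-only comparison uses fewer points and is less precise. As a guide, with a random intercept only, the variance of a 5-to-12-month slope from the two nurse visits is 42 / 24.5 = 1.71 times that from all eight. With an assumed slope SD of 0.05 Z per month and residual SD of 0.3 Z, the ratio is (0.05² + 0.3²/24.5) / (0.05² + 0.3²/42) = 1.33. Role separation does nothing for visits with a single coordinator, whereas the nurse-only comparison covers every infant measured at 12 months.
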